#### Data handling, storage, and archiving

The Chinese GCP regulation requires that all clinical trial documents must be kept for at least 5 years after completion or termination of the trial. The Shanghai Municipal Health Commission requires that all patient medical charts, including all imaging records, to be maintained for at least 7 years. The Research Unit and the Medical Record Unit of the Department of Medical Affairs of the SPHIC will be responsible for archiving the research documents and medical charts, respectively.

#### Interim analysis

To allow for early stoppage of the trial, in case of an observed overwhelming treatment effect, a group-sequential design will be applied with one interim analysis that is to be performed when 50% of the expected number of events under the null-hypothesis have occurred. Under the assumptions made in sample size calculation, the interim analysis will be performed after an occurrence of 92 events, which should happen approximately 26 months after the initiation of the recruitment. The stopping rule is specified according to O’Brien and Fleming [53].

No formal boundary for stopping for futility is specified. However, if the results of the interim analysis suggest that the objectives of the study cannot be reached with a feasible number of patients or that the benefit/risk ratio for the study has worsened markedly, the study may be stopped by the decision of the principle investigator. As in this case, the null-hypothesis would not be rejected, no type I error would be committed, and therefore the type I error rate of the study would still be controlled at 5%.

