### Ethics, informed consent, and safety

All clinical trials of the SPHIC, including the present trial, are required to adhere to the policies set forth by the Institutional Academic Committee and the Institutional Review Board (IRB). IRB approval of the current trial was obtained. The following sections were adapted and summarized from the institutional policies on human studies to which the present trial will adhere.

The IRB of the Shanghai Proton and Heavy Ion Center (SPHIC) independently monitor the recruitment, the reporting of adverse events, and the data quality for all clinical trials. Data and interim results for this trial will be reviewed semi-annually according to the trial protocol. The IRB will provide the principal investigator with requirements and recommendations on the modification of the trial, which may or may not include termination of the trial.

The study will be conducted according to the Chinese guidelines for good clinical practice (GCP) and the principles of the Declaration of Helsinki (2008 version, adopted at the 59th World Medical Association General Assembly, Seoul, Korea, October 2008).

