### Treatment assignment

The flow chart of this Phase I/III trial is illustrated in Fig. 2. Patients enrolled into Phase I of this trial will be assigned to groups of 3, and each group will receive a progressively increasing dose of induction CIRT boost until the safe dose is determined or the maximal dose of 18 GyE in 3 fractions is reached without ≥ grade 3 toxicities. Patients who later opt out of the study will be replaced by newly enrolled ones. Patients enrolling into the Phase III of this trial will be randomly assigned to either the experimental or control arm (1:1 randomization), as described above. Patients withdrawn from this phase will retain their randomization number, and new patients will be issued with a new randomization number.

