### Treatment after tumor progression

After completion of chemoradiotherapy, further treatment, including surgical resection, a second course of irradiation, systemic chemotherapy, or targeted therapy may be clinically necessary in case of disease recurrence or progression. These treatment decisions will be made at the discretion of the treating physician and/or team.

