#### Type I error rate and power

Time to death for any reason will be compared between the two arms in Phase III of this trial, using a two-tailed log-rank test at an overall type I error rate of 5%. The desired power is 80%. Sample size calculation is based on the unstratified log-rank test.

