#### Sample size calculation

For calculating the OS, assuming a median OS of 16 months in the control arm and 24 months in the experimental arm (corresponding to a hazard ratio of 0.67 or a reduction in the risk of death by 33%), 192 events are required to achieve an 80% power of the log-rank test at a two-sided overall α level of 5%.

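### The principal investigator may stop the trial on the interim results with no numerical guide; this implies access to the comparison and leaves the loss of power unbounded

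*Protocol article*

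**What the plan says.** The Interim analysis section plans one look, meant to allow an early stop for overwhelming efficacy. It says outright that futility has no formal boundary. It then names two grounds for stopping: the interim results suggest that the aims are out of reach with a realistic number of patients, or benefit/risk has become markedly worse. Neither has a number attached. On either ground, "the study may be stopped by the decision of the principle investigator". The only defence offered is that such a stop cannot produce a false positive, so the 5% level holds. Power is not mentioned there.

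The design figures are in other sections. Type I error rate and power says of the target, "The desired power is 80" per cent. Sample size calculation says that "192 events are required to achieve an 80% power of the log-rank test".

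On oversight, the Ethics, informed consent, and safety section makes the IRB the independent monitor and adds: "Data and interim results for this trial will be reviewed semi-annually according to the trial protocol". The IRB sends the principal investigator requirements and recommendations, which can extend to termination. The Interim analysis section does not mention the IRB.

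On care after recurrence, the section Treatment after tumor progression says: "These treatment decisions will be made at the discretion of the treating physician and/or team".

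**The concern.** Two things are at stake.

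**Knowledge of the results.** A decision that rests on the interim results requires seeing them, or a summary that gives them away. The article describes no masking, and the experimental arm has visibly more: the carbon ion boost, an additional blood sample and an additional scan two weeks after the boost starts. If the trial continues past the look, the person leading it would know the survival trend by arm while patients are still being enrolled, treated and followed. That can affect who is recruited, which treatment follows progression, when symptom-directed imaging is ordered (and hence PFS), and how response and toxicity are judged. The abstract lists toxicity as a primary endpoint.

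**Power.** A futility stop cannot raise type I error, so the protocol's argument is correct as far as it goes. The cost falls on type II error: some trials of a treatment that works would be stopped. With no threshold, the size of that cost depends on one person's judgement at the time, and the 80% figure does not allow for it.

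**Working it through.** **Inputs from the protocol article**
- Test: "using a two-tailed log-rank test at an overall type I error rate of 5" per cent (Type I error rate and power).
- Effect: "assuming a median OS of 16 months in the control arm and 24 months in the experimental arm", so HR = 16/24 = 0.667 (Sample size calculation).
- Allocation: "randomly assigned to either the experimental or control arm (1:1 randomization") (Treatment assignment).
- Looks: 96 and 192 OS events, two-sided alphas 0.003 and 0.049 (Outcome analyses).
- Accrual: 243 patients over 36 months (Anticipated duration of trial).
- The Interim analysis section gives 92 events and about month 26 for the look; both counts are carried below.

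**Step 1: reproduce the plan's figure.** Schoenfeld events = 4(1.96 + 0.8416)² / (ln 1.5)² = 191, against 192 stated. It reproduces.

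**Step 2: power of the two-look design with no futility stop.** With log-rank statistics Z1 and Z2:
- mean of Z1 = ln(1.5)·√(96/4) = 1.986
- mean of Z2 = ln(1.5)·√(192/4) = 2.809
- correlation = √(96/192) = 0.707
- critical values = 2.968 and 1.969

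Power = P(Z1 > 2.968) + P(Z1 ≤ 2.968 and Z2 > 1.969) = 0.163 + 0.637 = 80.1%. Overall two-sided alpha is 0.0500. The 80% is therefore the power when the clause is never used.

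**Step 3: power if the clause is used.** The protocol gives no threshold, so these rules are assumptions. A stop at an observed HR of h or above means stopping when Z1 ≤ −ln(h)·√24. For h = 0.80 this is Z1 ≤ 1.093. The second term in Step 2 is then integrated only above that value: 0.163 + 0.560 = 72.4%.

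| Assumed futility rule at 96 events | Power if HR = 2/3 | Loss (points) | Chance of a wrong stop |
|---|---|---|---|
| never used | 80.1% | – | – |
| interim HR ≥ 1.00 | 79.8% | 0.3 | 2% |
| interim HR ≥ 0.85 | 76.2% | 3.8 | 12% |
| interim HR ≥ 0.80 | 72.4% | 7.7 | 19% |
| current-trend conditional power < 10% (HR about 0.86) | 76.6% | 3.4 | 11% |
| current-trend conditional power < 20% (HR about 0.82) | 74.2% | 5.9 | 16% |
| current-trend conditional power < 50% (HR about 0.75) | 66.3% | 13.8 | 28% |

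Losses are taken before rounding. With the look at 92 events, power is up to about 0.6 points lower.

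**Step 4: who is still to be enrolled at the look.** Assume exponential survival, uniform accrual over 36 months and no dropout. By calendar month T ≤ 36, the expected events in an arm with hazard λ = ln 2/median are (243/2)/36 × [T − (1 − e^(−λT))/λ]. At month 26 the two arms together give 61 events (medians 16 and 24) or 70 (both 16), short of 92 or 96.

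| Medians (months) | Events | Month reached | Still to enrol, 243 × (36 − T)/36 |
|---|---|---|---|
| 16 and 24 | 96 | 33.9 | 14 (6%) |
| 16 and 24 | 92 | 33.1 | 20 (8%) |
| 16 and 16 | 96 | 31.4 | 31 (13%) |
| 16 and 16 | 92 | 30.6 | 37 (15%) |

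Enrolment is still open in every case, but near its end.

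**The case against.** Several counter-arguments have weight.

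- **Nothing says in words that the principal investigator is shown the comparison.** True. The IRB could review and recommend, and the principal investigator could then act. The two sections can coexist on that reading, so a reader who infers a flat contradiction goes too far. What stands is that the stopping clause rests on the interim results, names one decision-maker and leaves the IRB out.
- **An article condenses, and a firewall is the sort of detail left to a fuller document.** Fair for the missing firewall taken alone. But the clause is a rule that the article states, with its own justification, and that justification covers only half of the error rates.
- **The thresholds are invented.** They are. The clause speaks of aims that cannot be reached, which fits a poor result better than a mild shortfall, and at the strict end the loss is 0.3 points. A reader might infer that power really is 66% or 72%. The documents do not support that; they only fail to exclude it.
- **Overall survival is robust.** Largely so. The endpoint is death from any cause, analysed by intention to treat, and PFS is labelled exploratory. It would be wrong to infer that ascertainment of the primary efficacy endpoint is compromised.
- **Month 26 suggests that 28% of patients are still to come.** Taking that date at face value gives 243 × 10/36 = 67.5 patients. But the look is triggered by events, and the protocol's own survival assumptions place it about five to eight months later, with 6–15% left. The 28% should not be used.

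**Conclusion.** The point holds in a limited form. The protocol gives the principal investigator a discretionary stop on the interim results, sets no numerical guide, and defends it by an error rate that a futility stop does not threaten. That this person sees the comparison is an inference, though the natural one.

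The 80% power is correct only if the clause is never used (80.1%). Across the assumed rules, the loss runs from 0.3 points to about 14. It is unbounded by the plan rather than certain, and small under a strict reading.

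The bias concern covers recruitment of the last 14 to 37 of 243 patients (about months 31 to 34), post-progression treatment, PFS, response and toxicity grading. No size can be put on it from the documents. These results rest on HR 2/3, the stated alphas, the normal approximation to the log-rank test, and exponential survival with uniform accrual.

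**What to change.** 1. Amend the Interim analysis section so that the arm-level interim OS comparison goes to the independent reviewer already named in the Ethics section (the IRB), and the principal investigator receives only its recommendation.
2. Reconcile the two sections on who reviews and who decides.
3. Leave the IRB's access to deaths and safety data by arm unchanged at its semi-annual reviews. Withholding these would weaken safety monitoring.
4. For the futility ground, either give a non-binding guide with its power cost (for example, an observed HR of 1 or above, about 0.3 points) or state that 80% power assumes no discretionary futility stop. A non-binding guide still leaves discretion, so it documents the expected cost rather than guaranteeing the power.
5. Keep the benefit/risk ground as a separate safety judgement, not tied to the futility guide.

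The cost is protocol wording. It uses a body that the article already names and changes neither the event count nor the sample size. The IRB should confirm that it can review comparative efficacy, since the article lists its independent monitoring as recruitment, adverse-event reporting and data quality. The downside is that the principal investigator loses direct access to interim comparisons.

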## Discussion

The results of traditional tri-modality treatment of GBM (maximal safe resection, low-LET photon irradiation with concurrent TMZ) remain discouraging. The recent addition of the alkylating agent, TMZ, prolonged the median survival from 12 months to 15 months [1]. It was the first time that a change in treatment has lead to a statistically significant improvement in OS since the past several decades, but the efficacy is still not satisfactory. However, there have been no new equally substantial breakthroughs in the past 12 years since the release of the results from that study, despite exhaustive efforts to build upon its progress have been tried. Clearly, a more radical and “outside-of-the-box” strategy is needed.

Our proposed clinical trial is novel and may represent a first step in a new direction for several reasons. First, it uses CIRT, which has a multitude of physical properties that set itself apart from both the traditional photon-based irradiation and even the more widely-used, particle-based PRT. Like PRT, CIRT is characterized by a low dose deposition along the entry channel of the beam, with a steep dose deposition in the region of the Bragg peak, which by modulation of the beam energy and tissue compensation, can be focused over CTV. The rapid dose deposition fall-off, after the Bragg peak, allows for dose-sparing of normal tissue and non-targeted structures, significantly reducing toxicity. Unlike photon radiotherapy or PRT, CIRT poses both high-LET and RBE properties, which translate into more efficient tumor cell killing (even in conditions of hypoxia and against low-LET resistant tumors) and via distinct mechanisms, which have been shown to be anti-tumor immunogenic and to induce abscopal effects.

Second, and perhaps the most important reason, is that CIRT is used as a boost prior to the initiation of the standard treatment course, which consists of low-LET PRT with concurrent TMZ. The special timing of the boost will take full advantage of the unique characteristics of CIRT. From a tumor cell population perspective, the postoperative setting, before the initiation of adjuvant radiotherapy, represents the point in time when the number of residual cells is the largest and when the hypoxia levels are at their greatest. Therefore, it can be theorized that this is when the more efficient tumor cell-killing CIRT should be used since its biological impact will not be hindered by hypoxia. Further, large fractions of this high-LET irradiation, when applied to radio-naïve cells (including glioma stem cells), will result in a more robust initial cell-killing effect. In the absence of immunosuppressive effects of TMZ, we anticipate that the immunogenic response will shift the balance from a pro-tumor immunity (common in GBM) to an anti-tumor immunity and will proceed unperturbed.

The abscopal effect, observed to be induced when CIRT is applied to other tumors may have importance in GBM. The diffuse, infiltrative nature of glioma cells create a scenario where the tumor and tumor-initiating cells are disseminated throughout the brain parenchyma, outside of radiotherapeutic target volumes, and can evade lethal doses of irradiation. Further, they can migrate towards the primary tumor site and initiate tumor recurrence [54]. It is tempting to speculate that the immunogenic nature of CIRT could create an abscopal effect within the brain’s distinct immune system and that these malignant cells could be more efficiently cleared by anti-tumor immunity. We anticipate that this phenomenon will contribute towards improved outcomes for the patients enrolled in the experimental arm of the Phase III of this trial.

The Phase I of this trial allows for the inclusion of AA patients. This is permissible for several reasons. Patients with AA are treated in an identical fashion at our institution, and the purpose of the Phase is to determine the maximal safe dose of CIRT boost, which is not dependent upon the histology of the tumor. However, AA patients are excluded from Phase III of this trial, as their expected median OS ranges from 2 to 3 years, which are significantly longer than that of GBM patients, and their inclusion within the statistically-weighted study design could interfere with the final study results.

In summary, the CIRT boost delivered prior to standard chemoradiotherapy is a novel therapeutic approach for GBM. It uses the relatively new modality of radiotherapy. In addition, the timing of its delivery seeks to maximize the physical, biological, and immunologic advantages that CIRT has over the more traditional, low-LET radiotherapies.

## Abbreviations

AA: anaplastic astrocytoma
BED: biological effective dose
CIRT: carbon ion radiotherapy
CTV: clinical target volume
CR: complete response
DLT: dose-limiting toxicity
ELISA: enzyme-linked immune-sorbent assay
EQD2: equivalent dose for a 2 Gy/fraction treatment
FLAIR: fluid-attenuated inversion recovery
GBM: glioblastoma
GCP: good clinical practice
GTV: gross-tumor volume
GyE: gray equivalents
HIT: Heidelberg Ion-Beam Therapy Center
IL: interleukin
IRB: Institutional Review Board
ITT: intention to treat
LET: linear-energy-transfer
MET/FET PET: C-Methionine/18F-fluoro-ethyl-tyrosine positron emission tomography
*MGMT*: O-6-methylguanine-DNA methyltransferase
MTD: maximal tolerable dose
MRS: magnetic resonance spectroscopy
NIRS: National Institute of Radiological Sciences
OAR: organ-at-risk
OS: overall survival
PCR: polymerase chain reaction
PRT: proton radiotherapy
PR: partial response
RBE: relative biological effectiveness
SD: stable disease
SPHIC: Shanghai Proton and Heavy Ion Center
TGF-β: transforming growth factor beta
TNF-α: tumor necrosis factor α
